#### Dietary intake

Daily food intake will be monitored through the use of a validated, self-reported food diary [64] and a food frequency questionnaire. Completion of the food diary will require participants to record everything they eat and drink over a specified seven-day period. In order to clarify the foods and drinks that are consumed, the food frequency questionnaire will include 12 semi-quantitative items. Participants will be asked to complete the questionnaire and food diary in their own home after a 45 minute oral training session to help describe intake and estimate portion size. The collated data will be analyzed using nutritional analysis software by Health Options Ltd (Nutri Check, Health Options Ltd, Cirencester, Gloucester, UK). Values for the nutrient amounts in foods will be obtained from McCance and Widdowson's the Composition of Foods [64]. Participants will be encouraged to continue their normal eating and drinking habits throughout the intervention.

#### Environmental audit

The Secondary School Environmental Audit tool [65] will be used to assess the school as a setting for promoting healthy eating and PA. This will include assessment of the physical (what is available), economic (what are the financial factors), policy (what are the rules) and socio-cultural (what are the attitudes, beliefs and perceptions) environments in relation to nutrition, PA and the promotion of healthy body size. The self completing audit tool comes in three parts with the relevant part being sent to the deputy principal, canteen manager and three teachers as recommended [65]. Preventing overweight and obesity requires understanding and changing of the obesogenic (obesity promoting) environment in which individuals frequent. Thus, this audit will be able to identify environmental factors that promote unhealthy weight gain and help inform future interventions.

#### Observational analysis

Observational data will be gathered by video recording all sessions. Direct behavioural observation can provide contextually rich data and is cited as the criterion measure of paediatric PA behaviour [66]. By doing so we will be able to see not only quantitative measurements such as distance covered and the variability of pace within and between the 30 s maximal effort sprints, but also how the exercise protocols affect participants through different communication, responses, behaviours and actions. In addition, critical moments such as 'drop out' could be assessed and evaluated. Finally, with the synchronisation of video with HR, effects of various constraints such as feedback, peer, teacher and researcher influence could be evaluated within, between and across sessions.

#### Feedback to participants

This feedback will include the results of all pre and post measurements; how individual results compare to the desirable level for this age group; and guidance on how unfavourable measures might be improved through lifestyle changes. Feedback will also be given to relevant teaching staff, on group, but not individual, findings. This will provide the school with invaluable information on the general health and well-being of their pupils which can help inform future interventions.

#### Sample size

In order to determine sensitivity to change, sample size will be estimated using the procedures of Park and Schutz [67] for ANOVA designs that incorporate a repeated factor. For a medium effect size in the intervention groups of d = 0.50, power of .80 (suggesting an 80% probability of achieving significance at the *p *= .05 level) this is achieved with a group size of 17 participants. Effect sizes > 0.5 indicate clinically relevant changes [68]. Assuming a drop-out rate of 30%, this would require an initial recruitment of 24 participants per group. The intervention will be carried out during the lunch hour or PE lessons, on Monday, Wednesday and Friday, and for a period of 8 weeks. The interventions will be performed in the school sports hall; led initially by the research team and then by the PE teacher; and during January through May, 2009, to allow for uninterrupted use of the facilities.

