### Data Analysis

A pre- and post-intervention design will be used to compare differences in measured outcomes between participants assigned to the control group and the intervention groups. Initially, baseline data will be used to perform Pearson's product moment correlation coefficients, followed by multiple regression analysis to estimate the significance of selected predictors on CVD risk factors. Statistical significance will be set at *P *= 0.05.

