### Intervention

Participants involved in the intervention will be assigned to groups A or B by a third party using computer generated sequences of random numbers. The research team and the participants will be blinded to the randomization process, and assignment to groups will only be disclosed after baseline testing. All participants will be instructed not to change their dietary or lifestyle habits other than prescribed. The secondary 5 participants will act as the control group and will be assigned to group C (*n *= 24). Participants will be encouraged to continue their regular PA patterns.

Group A (*n *= 24) will be instructed to complete a 30 seconds (s) maximal effort sprint within a 20 m distance separated by cones (see Figure 1). The start point will be located at the mid-point of the markers. Participants will be instructed to sprint from the midpoint to the first marker, turn, and then sprint 20 m in the opposite direction to the second marker. Thereafter, participants will turn and run again through the midpoint covering a total distance of 40 m. Though this protocol has been used and validated as a measure of anaerobic performance [47], in this study, participants will be instructed to sprint maximally for a period of 30 seconds. Following 30 s rest, the participants will be instructed to repeat this procedure a further 3 times. This equates to 2 minutes (mins) of maximal effort sprinting interspersed with 2 mins recovery. Participants will be requested to perform this protocol 3 times weekly. Training progression will be implemented by increasing the number of repeats from four repetitions during weeks 1 and 2, to five repetitions during weeks 3 and 4, to six repetitions during weeks 5 and 6. Finally, during week 7 participants will still perform six repetitions but interspersed by only 20 s recovery. Prior to the commencement of the training regime, participants will be given a familiarization trial of four low intensity runs under test procedures.

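### The stated 80% power for d = 0.50 with 17 per group fits a pre-post change, not the control-versus-intervention comparison, where power is about 29% to 61% at assumed pre-post correlations of 0.5 to 0.8

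*Protocol article*

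**What the plan says.** The Sample size section of the protocol article aims at sensitivity to change and uses a published procedure "for ANOVA designs that incorporate a repeated factor". It continues: "For a medium effect size in the intervention groups of d = 0.50, power of .80", which it explains as "suggesting an 80% probability of achieving significance at the" 5% level, and concludes that "this is achieved with a group size of 17 participants". Allowance for losses follows: "Assuming a drop-out rate of 30%, this would require an initial recruitment of 24 participants per group". The same paragraph treats effect sizes above 0.5 as clinically relevant. It does not say whether d is a change over time or a difference between groups, which SD standardises it, or what pre-post correlation was used.

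The Data Analysis section says that the pre-post design will "compare differences in measured outcomes between participants assigned to the control group and the intervention groups". The Intervention section sets up three groups of 24. Groups A and B are randomised from secondary 6. For the third, "The secondary 5 participants will act as the control group and will be assigned to group C".

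**The concern.** A power statement is normally read as applying to the comparison that the trial will make. Here that comparison is between groups. With no more than 17 completers per arm, a medium between-group effect is ordinarily well out of reach unless baseline and follow-up are very highly correlated.

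Because the same paragraph ties an effect of about 0.5 to clinical relevance, the stated 80% invites a reader to take a non-significant group comparison as evidence against a relevant effect. If true power is 29% to 61%, a real 0.50 SD difference would be missed in 39% to 71% of such trials.

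**Working it through.** **Inputs from the article:** d = 0.50, power 0.80, significance level 0.05, 17 completers per group. **Assumptions:** two-sided test; pre-post correlation r from 0.5 to 0.9; equal SD at both times; d in outcome SD units. All powers use the noncentral t distribution.

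**1. Reproducing the stated figure.** Take a 0.5 SD pre-post change pooled over two groups of 17 at r = 0.5.
- SD of change = √(2(1 − r)) = √(2 × 0.5) = 1.0 outcome SD.
- Noncentrality = (0.5/1.0) × √34 = 2.92, with 34 − 2 = 32 degrees of freedom.
- Power = 0.807. With 16 per group it is 0.781, so 17 is the smallest group size that reaches 80%.

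The stated 17 is therefore obtainable at exactly the stated d, as a time effect over two groups. Numerically the same result arises for a two-group, two-time interaction at f = 0.25, but with r = 0.5 that means a between-group difference in change of 1.0 SD. For pre-post change within a single group of 17, power is 49% at r = 0.5 and 71% at r = 0.7, and 80% needs r of about 0.76.

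**2. The between-group comparison.**
- Change scores: noncentrality = [0.5/√(2(1 − r))] × √(17/2), with 32 degrees of freedom.
- Baseline-adjusted analysis: replace √(2(1 − r)) by √(1 − r²), with 31 degrees of freedom.

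For r = 0.5 with change scores: 0.5 × √8.5 = 1.46, power 0.293. For r = 0.8: (0.5/0.632) × √8.5 = 2.30, power 0.608.

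| Assumed r | Power, change score | Power, baseline-adjusted | Completers per group for 80%, change score (adjusted) |
|---|---|---|---|
| 0.5 | 29% | 37% | 64 (49) |
| 0.7 | 45% | 51% | 39 (34) |
| 0.8 | 61% | 65% | 27 (24) |
| 0.9 | 89% | 90% | 14 (13) |

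Solving for r at 17 per group, 80% power is reached at r = 0.873 with change scores and 0.864 with baseline adjustment. If all 24 recruits per group completed, change-score power would be 40% at r = 0.5 and 76% at r = 0.8.

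**3. Detectable difference.** With 17 per group, 80% power corresponds to 0.991 SD of the change score. In outcome SD this is 0.991 × √(2(1 − r)):
- r = 0.5: 0.991 × 1.000 = 0.99
- r = 0.7: 0.991 × 0.775 = 0.77
- r = 0.8: 0.991 × 0.632 = 0.63

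All three exceed 0.50.

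**The case against.** The strongest reply is that the calculation is sound for what it says it does. It speaks of sensitivity to change, a repeated factor, and an effect in the intervention groups, in the plural. There are two such groups, and step 1 returns 17 at exactly d = 0.50. This stands. A reader might infer an arithmetic slip, or that the effect size was doubled by mistake; the documents support neither, because a plain time effect over two groups gives the same number with no doubling. What it does not do is turn that figure into power for comparing groups. A pooled pre-post change cannot separate high-intensity training from control or from moderate exercise.

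Second, the correlation is not in the article, the cited method paper cannot be inspected, and a condensed article may leave such inputs to a fuller document. This also stands: the missing correlation is not a fault in itself, and at r of about 0.87 or more the stated 80% does hold between groups. The point is that a stated power figure does not match the stated comparison over a wide range of correlations.

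Third, the study describes itself as a pilot and nowhere says that null results will be read as excluding an effect. That is fair. The misreading is a risk that the wording creates, not a stated intention.

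**Conclusion.** The point holds as a mismatch between the powered effect and the planned contrast. The 80% figure is consistent with a 0.5 SD pre-post change. For a between-group difference of 0.50 outcome SD, 17 completers per group give 29% to 61% power with change scores, or 37% to 65% with baseline adjustment, at assumed correlations of 0.5 to 0.8.

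Two stronger conclusions are tempting and are not supported. One is that the design can detect only about 1.0 SD: that is true in SD of change, but in outcome SD it holds only near r = 0.5 and falls to 0.63 at r = 0.8. The other is that power is inadequate for most of the listed outcomes: the article gives no correlation for any outcome, so this cannot be said. The results rest on a two-sided 5% test, equal SDs at both times and the assumed correlations.

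**What to change.** Keep enrolment at 24 per group and revise the Sample size paragraph to:

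- say that the 80% figure refers to pre-post change, if that is what was computed;
- name the contrast, the SD used as standardiser and the assumed pre-post correlation;
- add the between-group figures in outcome SD, for instance: with 17 completers per group and a two-sided 5% test on change scores, power for a 0.50 SD difference between two groups is about 29%, 45%, 61% and 89% at correlations of 0.5, 0.7, 0.8 and 0.9, and the difference detectable with 80% power is 0.99, 0.77 and 0.63 SD at correlations of 0.5, 0.7 and 0.8;
- no longer present 80% power for d = 0.50 as applying to the comparison of groups.

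The cost is a rewritten paragraph and a less favourable power statement. No participants, measurements or analyses need to change.

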## Discussion

It is well established that regular PA has beneficial effects on the health and well-being of youth [37]. Nevertheless, current levels of PA are widely regarded as insufficient to meet current guidelines[19], with lack of time often cited as a contributing factor[43]. Health promotion interventions that aim to modify environmental factors that influence behaviour have now become an integral focus of emerging research being undertaken in the school environment. We fully embrace the concepts afforded through ecological models and have thus developed a comprehensive intervention approach that will target several influences of behaviour. Thus, in this study we aim to provide a comprehensive school based intervention strategy that will aim to determine whether HIT can elicit CVD protection in adolescents.
